### Study outcome measures

The following outcomes will assess the feasibility of a phase III RCT of nVNS to reduce ileus:

Proportion of eligible patients identified from screening logs.Number of eligible patients randomised (per month) and reasons for approach failure.Adequacy of participant blinding according to a blinding poll (Bang Blinding Index).^17^Compliance to the preoperative and postoperative stimulation schedules according to participant-reported diaries (maximum of 10 stimulations before and after surgery).Incidence of complications and serious complications within 30 days.Proportion of missing clinical outcome data, withdrawals and loss to follow-up.

Progression will be determined using the parameters outlined in table 2. ‘Progress’ outcomes will build a case for progression to a phase III trial. ‘Adjust’ outcomes will build a case for progression after appropriate amendments have been made. ‘Stop’ outcomes will contraindicate a case for progression, unless modifiable barriers are identified and further assessments of feasibility are undertaken. The predominance of such outcomes will be considered by the research team in the decision-making process.

**Table 2 T2:** Progression criteria

Criteria	Stop	Adjust	Progress
Proportion of eligible patients identified from screening logs	<10%	10%–20%	>20%
Number of eligible patients randomised over 24 months (site: SJUH)	≤2 per month	3–4 per month	≥5 per month
Number of eligible patients randomised over 18 months (site: BRI)	<1 per month	1–2 per month	≥3 per month
Adequacy of participant blinding (according to Bang Blinding Index)	Index <−0.5 Or index >0.5	Index −0.2 to −0.5 Or index 0.2–0.5	Index 0 to −0.19 Or index 0–0.19
Average compliance to the study treatment schedule	<10/20 stimulations across 10 days	10–15/20 stimulations across 10 days	≥16/20 stimulations across 10 days
Proportion of missing clinical outcome data	>40%	15%–30%	<15%
Proportion of randomised patients lost to follow-up	>40%	15%–30%	<15%
Incidence of complications or serious complications	>20% increase in complications	5%–20% increase in complications	<5% increase in complications

BRI, Bradford Royal Infirmary; SJUH, St James’s University Hospital.

Clinical data will be collected to explore variability in candidate measures including number of postoperative days to first flatus, first stool, first oral intake, hospital discharge and GI-2 (composite outcome of passage of stool and oral tolerance).^18^

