### Statistical analysis plan

All analyses will follow a pre-determined statistical analysis plan^20^ and will be overseen by a qualified medical statistician. Recruitment, baseline characteristics, compliance and outcome data will be presented descriptively as rates (categorical) and means (continuous) with 95% CIs. No formal statistical hypothesis testing across randomised groups will be conducted. Groups may be collapsed to pre-surgery and post-surgery stimulus versus sham and reported descriptively. Blinding will be analysed according to the Bang Blinding Index, with an index of >0.2 representing unblinding, −0.2 to 0.2 representing random guesses and <−0.2 representing opposite guessing (also considered a source of unblinding).^17^ All analyses will be performed for intention-to-treat (treatment as randomised) and per-protocol populations. Possible reasons for exclusion from the per-protocol population include non-compliance to the device schedule (defined as any deviation from the 5-day preoperative and postoperative stimulation schedule), conversion from laparoscopic to open surgery, formation of unplanned stoma, return to theatre prior to the return of bowel function and randomisation errors. The trial will be reported according to the Consolidated Standards of Reporting Trials Checklist.^21^

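### Two Table 2 progression rows, missing outcome data and loss to follow-up, assign no verdict to results above 30% and up to 40%

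*Protocol article*

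**What the plan says.** The section Study outcome measures states that "Progression will be determined using the parameters outlined in table 2". Two of the eight rows of Table 2, "Proportion of missing clinical outcome data" and "Proportion of randomised patients lost to follow-up", carry the same limits: Stop >40%, Adjust 15%–30%, Progress <15%. The text below the definitions of the three verdicts adds that the research team will consider which kind of outcome predominates.

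On blinding, Table 2 gives Stop as "Index <−0.5 Or index >0.5", Adjust as "Index −0.2 to −0.5 Or index 0.2–0.5" and Progress as "Index 0 to −0.19 Or index 0–0.19". The section Statistical analysis plan interprets the same index differently at the boundary: "with an index of >0.2 representing unblinding, −0.2 to 0.2 representing random guesses and <−0.2 representing opposite guessing".

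**The concern.** A set of progression bands should give every possible result exactly one verdict. In these two rows the top of Adjust (30%) and the bottom of Stop (40%) do not meet. The other percentage rows do meet: screening eligibility runs <10%, 10%–20%, >20%, and complications run <5%, 5%–20%, >20%. So the 10-point hole looks like a slip in one of the two limits, and the article does not show which one.

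The hole separates going ahead with amendments from not going ahead. The trial exists to inform that decision and plans no hypothesis tests between randomised groups, so Table 2 is its main pre-set decision rule. If a result falls in the hole, someone has to decide what the rule was after seeing the data.

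**Working it through.** **Inputs.** Total randomised: 140, from Sample size (4 arms × 35 = 140, which reproduces the stated total). Band limits: 15%, 30% and 40%, from Table 2.

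**Limits as counts out of 140.**
- 15%: 0.15 × 140 = 21
- 30%: 0.30 × 140 = 42
- 40%: 0.40 × 140 = 56

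**Loss to follow-up, bands as printed.**

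| Number lost | Proportion | Verdict |
|---|---|---|
| 0–20 | up to 14.3% | Progress |
| 21–42 | 15.0%–30.0% | Adjust |
| 43–56 | 30.7%–40.0% | none |
| 57–140 | 40.7% and above | Stop |

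The unclassified run has 56 − 43 + 1 = 14 counts. Exactly 30% is Adjust. Exactly 40% is unclassified, because Stop begins strictly above it. The missing-data row has the same percentage gap; its counts depend on the denominator used for that proportion.

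**Chance of landing in the gap.** The article states no expected loss rate, so a range is assumed. With X ~ Binomial(140, p), the chance is P(43 ≤ X ≤ 56):

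| Assumed true rate p | P(no verdict) |
|---|---|
| 20% | 0.2% |
| 25% | 7% |
| 30% | 45% |
| 35% | 78% |
| 40% | 53% |
| 45% | 13% |

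**What closing the gap does.**
- Adjust 15%–40%, Stop >40%: Progress 0–20, Adjust 21–56, Stop 57–140.
- Adjust 15%–30%, Stop >30%: Progress 0–20, Adjust 21–42, Stop 43–140.

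Both options classify every count. They differ only for 43 to 56 lost, where one gives Adjust and the other gives Stop.

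**Blinding index at the boundary.** An index of exactly 0.2 can occur, for example 7/35 or 14/70. Table 2 places it in Adjust, while the Statistical analysis plan section reads it as random guessing. The same holds at −0.2. The two sections disagree at these two points.

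**The case against.** **The criteria are not binding.** Outcomes build a case, a Stop can give way if modifiable barriers are found, and the team weighs the balance over eight rows. This stands in part. It rules out saying that the gap removes the protection of pre-set criteria: only the choice between Adjust and Stop is open, on two rows, and Progress is excluded. But weighing verdicts presupposes that each row has one, and the clause does not supply one for an unclassified value.

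**Heavy loss is unlikely over 30 days of follow-up.** That may be so, and the table above shows that the gap is almost unreachable at a true rate of 20%. The authors nevertheless chose to set thresholds at 30% and 40%, so the rule should work there.

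**The unseen analysis plan may settle it.** The table is printed with its limits. A document that closed the gap would have to differ from it.

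**Stronger readings that the article does not support.** A reader might infer that the whole table is full of holes, because monthly recruitment (2 to 3 and 4 to 5 at the Leeds site, 2 to 3 at Bradford) and mean compliance (15 to 16 of 20) are banded in whole numbers, and because nothing covers an index between 0.19 and 0.20. Rounding to the unit shown resolves all of these, and a rounding convention is a detail that an article may leave to the full protocol or analysis plan. Rounding cannot resolve a 10-point gap.

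A reader might also infer that the two blinding statements give conflicting progression decisions. They do not. Table 2 governs progression, so ±0.2 is Adjust; the analysis section supplies an interpretive label only. Nor can a firm probability be attached to an index of exactly ±0.2, since that would need the number of poll responses and of don't-know answers, which the article does not give.

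**Conclusion.** The point holds for two of the eight rows. As printed, missing clinical outcome data or loss to follow-up above 30% and up to 40% has no verdict. For loss to follow-up with all 140 randomised, this is 43 to 56 participants. The gap follows from the printed limits alone. Only its likelihood rests on assumptions: a binomial count and a true loss rate that the article does not state. It becomes likely only if true loss is about 30% or more.

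The mismatch at a blinding index of ±0.2 is real but minor: one boundary point and its mirror image, with Table 2 deciding progression. The whole-number bands are not an error.

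The rows should be corrected. Because the criteria are partly discretionary and the ambiguity lies only between Adjust and Stop, this is not a flaw that invalidates the plan.

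**What to change.** Before results are known, give the two rows one shared cut-off, and have the sponsor state which was intended:
- Progress <15%, Adjust 15%–40%, Stop >40%; or
- Progress <15%, Adjust 15%–30%, Stop >30%.

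In the same edit, align the blinding limits. Either write Table 2 as Progress for an absolute index up to and including 0.2, Adjust above 0.2 and up to 0.5, Stop above 0.5; or change the limits in the Statistical analysis plan section to match Table 2.

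Optional tidying: write the recruitment and compliance bands as continuous ranges, or add one sentence on rounding.

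The cost is a rewording of Table 2 and perhaps one sentence elsewhere. It needs no extra participants, data or analysis.

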### Participant timeline

The timing of study procedures, clinical assessments and collection points are summarised in table 3. Participants will attend a preintervention study visit, where a trained investigator will provide an interactive tutorial on how to self-administer the device. This will provide an opportunity to practice self-administration under direct supervision. Allocation of study devices will take place at two timepoints. The first will take place at the pre-intervention study visit, where devices will be provided for use in the community. On admission to hospital, these will be collected and switched with the postoperative device. Throughout the stimulation schedule, participants will record their compliance to the device schedule using stimulation diaries. Gastrointestinal function will be recorded daily, as reported by patients. On the last stimulation day, participants will complete a poll to explore the performance of blinding before and after surgery. Follow-up data (including the occurrence of complications and serious complications) will be collected 30 days after surgery to capture events, which may occur during the index hospital admission or after discharge.

**Table 3 T3:** Schedule of events

	Events	Baseline	Preop study visit	5 days before surgery	Day of surgery (preop)	Day of surgery (intraop)	POD 1	POD 2	POD 3	POD 4	POD 5	POD 6–10	After discharge	30-day phone F/U
Study procedures	Trial consent	✓	✓											
	Device training		✓											
	Device distribution		✓		✓									
	Self-administered stimulation			✓			✓	✓	✓	✓	✓			
	Stimulation diary			✓			✓	✓	✓	✓	✓			
	Blinding poll										✓			
Data collection	Eligibility CRF	✓												
	Baseline CRF	✓												
	Operative CRF					✓								
	Gastrointestinal function CRF						✓	✓	✓	✓	✓	✓		
	Follow-up CRF													✓
Substudies*	*Optional substudy consents*	✓												
	Inflammatory response study Blood only: ✓; blood and fluid: ✓✓				✓	✓✓	✓		✓					
	*Small bowel motility study (MRI*)		✓						✓					
	*Qualitative substudy (participant or non-participant interview*)												✓	

*Substudies are optional and undertaken at the lead site only.

CRF, case report form; F/U, follow-up; POD, postoperative day.

### Sample size

As a feasibility study, no formal power calculation has been performed. In this four-arm parallel-group design, 35 participants per arm will allow robust estimates of variability in continuous clinical outcomes, and 70 patients randomised to pre-surgery and post-surgery groups will allow robust estimates of recruitment parameters.^19^ The total sample size of 140 allows robust exploration of both clinical and recruitment-related objectives.

### Recruitment

Participants will be approached with written information in the outpatient departments of St James’s University Hospital and Bradford Royal Infirmary. Research staff will be available to discuss the study over the phone, as well as opportunities to meet in person during patients’ routine schedule of pre-assessment and anaesthetic review appointments. Consent for participation in the study will be gathered using the approved consent form (online supplemental file 3).

10.1136/bmjopen-2020-046313.supp3Supplementary data

### Randomisation and allocation

Following confirmation of written informed consent, participants will be randomised to one of four intervention arms. The randomisation list will be prepared by an independent statistician using block randomisation with a variable block size. This will be stratified for type of colorectal resection (right-sided and left-sided) and recruitment centre. Randomisation will be facilitated centrally using an online 24-hour service and will be performed by study investigators.

### Blinding

Participants will be blinded to the study intervention before and after surgery. This is made possible through the use of a sham stimulator device, which is identical in appearance, weight and user interface, as well as being designed to provide a perceptible sub-therapeutic stimulation. All devices will be switched irrespective of whether the type of device (active or sham) remains constant throughout the pre-operative and post-operative schedules. Investigators and clinical outcome assessors will be unblinded to the intervention. Since outcomes relating to gastrointestinal function are patient-reported, the risk of assessor bias is considered to be low.

### Data collection and management

All trial data will be prospectively entered onto case report forms by dedicated research staff (a clinical research fellow and research nurses). Physical data will be stored in a restricted-access research unit, accessible only to the research team. All electronic data will be stored in pseudo-anonymised format at the University of Leeds according to sponsor requirements. As a feasibility study, a data monitoring committee is not planned.

### Statistical analysis plan

All analyses will follow a pre-determined statistical analysis plan^20^ and will be overseen by a qualified medical statistician. Recruitment, baseline characteristics, compliance and outcome data will be presented descriptively as rates (categorical) and means (continuous) with 95% CIs. No formal statistical hypothesis testing across randomised groups will be conducted. Groups may be collapsed to pre-surgery and post-surgery stimulus versus sham and reported descriptively. Blinding will be analysed according to the Bang Blinding Index, with an index of >0.2 representing unblinding, −0.2 to 0.2 representing random guesses and <−0.2 representing opposite guessing (also considered a source of unblinding).^17^ All analyses will be performed for intention-to-treat (treatment as randomised) and per-protocol populations. Possible reasons for exclusion from the per-protocol population include non-compliance to the device schedule (defined as any deviation from the 5-day preoperative and postoperative stimulation schedule), conversion from laparoscopic to open surgery, formation of unplanned stoma, return to theatre prior to the return of bowel function and randomisation errors. The trial will be reported according to the Consolidated Standards of Reporting Trials Checklist.^21^

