### Intervention

nVNS will be self-administered by participants using the gammaCore device (electroCore, New Jersey, USA). This provides a transcutaneous electrical stimulation comprising of 5×5 KHz sine wave complexes delivered over 1 ms and repeated at 25 Hz (maximum voltage: 24 V; maximum output current: 60 mA). The surface landmark of the carotid pulse is used to guide positioning of the device over the cervical vagus nerve. Participants will self-administer the device twice daily for 5 days before and after surgery, with each administration lasting for 2 min on either side of the neck. Participants will be instructed to adjust the stimulation setting to the maximum tolerated level. A sham device identical in appearance will be used as a control. This produces a subtherapeutic stimulation (0.1 Hz biphasic direct current) while providing a perceptible stimulation sensation.

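### The symmetric Bang index bands class a sham that convinces both groups equally as unblinded, because the active and sham indices are not read as a pair

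*Protocol article*

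**What the plan says.** The Statistical analysis plan section interprets the Bang Blinding Index "with an index of >0.2 representing unblinding, −0.2 to 0.2 representing random guesses", and adds a third category, "<−0.2 representing opposite guessing (also considered a source of unblinding".

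Table 2 (Study outcome measures) turns this into a progression criterion, "Adequacy of participant blinding (according to Bang Blinding Index". The bands are:

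- Progress: "Index 0 to −0.19 Or index 0–0.19"
- Adjust: "Index −0.2 to −0.5 Or index 0.2–0.5"
- Stop: "Index <−0.5 Or index >0.5"

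Neither place names the device group or period to which the index belongs, or says how an active and a sham index are to be read together.

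The Intervention section describes a sham that delivers a subtherapeutic current "while providing a perceptible stimulation sensation". On timing, the Participant timeline section states: "On the last stimulation day, participants will complete a poll to explore the performance of blinding before and after surgery". Table 3 ticks the poll on postoperative day 5 only. The preoperative device is exchanged for the postoperative one on admission.

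**The concern.** The Bang index is calculated within a group, as the share guessing correctly minus the share guessing incorrectly. Its sign in one group has no fixed meaning until it is set beside the other group. A negative index in the sham group means that sham users mostly believe they hold an active device, which is what a convincing sham should produce. If active users hold the same belief to the same degree, the allocation has not leaked.

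A rule that scores each index by its distance from zero cannot tell this pattern from genuine unmasking. Blinding is one of the six stated objectives and one row of the progression table. A misclassification there could lead the team to alter a sham that needs no alteration, or could weigh against a phase III trial for the wrong reason.

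The single late poll is a lesser matter. By postoperative day 5 the participant has had surgery, has used a second device and has several days of recovery to judge by. All of these can colour the guess about the first device.

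**Working it through.** **Inputs.** The bands are those of Table 2. Under Sample size there are 35 participants per arm, and two arms share each device type in each period, so 2 × 35 = 70 hold an active and 70 a sham device before surgery, and likewise after. The cut-offs are set rather than derived, so there is no figure of the plan to reproduce. The documents give no guess rates, so those below are assumptions shown over a range.

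**Step 1: indices when belief does not depend on the device.** Let a share q guess active and a share r guess sham in both groups, the rest answering 'don't know'.

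- Active index = q − r
- Sham index = r − q
- Sum = 0

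With no 'don't know' answers, r = 1 − q, so the indices are 2q − 1 and 1 − 2q.

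| Guess active / sham / don't know (both groups) | Active index | Sham index | Table 2 |
|---|---|---|---|
| 50 / 50 / 0 | 0.00 | 0.00 | Progress |
| 60 / 40 / 0 | +0.20 | −0.20 | Adjust |
| 70 / 30 / 0 | +0.40 | −0.40 | Adjust |
| 70 / 10 / 20 | +0.60 | −0.60 | Stop |
| 80 / 20 / 0 | +0.60 | −0.60 | Stop |

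With no 'don't know' answers, Stop needs 2q − 1 > 0.5, that is q > 0.75.

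**Step 2: comparison with true unmasking.** If 80% in each group guess correctly, both indices are 0.80 − 0.20 = +0.60, which is also Stop. The sums separate the cases: +0.60 − 0.60 = 0 against +0.60 + 0.60 = 1.20. The rule as written does not use the sum.

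**Step 3: how often the bands would be reached.** Exact binomial probabilities, 70 per device, no 'don't know' answers, guessing unrelated to allocation:

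- q = 0.8: each index falls in Stop with probability 0.852.
- q = 0.7: each index reaches ±0.2 with probability 0.972.
- In the same setting, the between-device difference in the share guessing active reaches ±0.2 with probability 0.022, 0.020, 0.013 and 0.004 at q = 0.5, 0.6, 0.7 and 0.8.

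**Step 4: chance alone, q = 0.5.** Counting exactly 0.2 as Adjust, as Table 2 does, an index reaches ±0.2 with probability 0.120 at n = 70 and 0.311 at n = 35. Counting exactly 0.2 as random guessing, as the Statistical analysis plan section does, gives 0.072 and 0.175. If 20% or 40% answer 'don't know', the Table 2 figure at n = 70 falls to 0.07 or 0.04. Stop by chance has probability of at most 0.002. The main point does not rest on this step.

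**Step 5: would averaging the two indices repair the rule?** If all active users identify their device and sham users guess at random, the indices are +1.0 and 0. Their mean is 0.5, which is Adjust; with sham users guessing at random, the mean could never reach Stop. A pair of +0.38 and 0 averages 0.19, which is Progress. Averaging therefore hides unmasking confined to one group.

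**Step 6: the poll.** The first device is handed back on admission and the only poll is on postoperative day 5, so the preoperative guess is recalled at least five days later. In the two mixed arms (sham then active, active then sham) the participant has felt both devices and can revise the earlier guess by comparison.

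**The case against.** The strongest defence is that opposite guessing is openly named as a category of its own, with a cited source, and that shared belief in active treatment deserves attention. The Discussion itself notes that sham controls in nerve stimulation studies can be associated with improved outcomes. That is a good reason to report shared belief. It is not a reason to classify it as unblinding, which concerns whether guesses track allocation.

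A second defence is that the analysis plan, which is not shown, may say how the indices are combined. It may. But the article itself fixes the bands and the label for negative values, and a joint reading elsewhere would have to override them.

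Three stronger readings are tempting and are not supported:

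- *A convincing sham is scored as failure, or would halt the programme.* Indices of 0.2 to 0.5 in either direction are Adjust, which allows progression after amendment. Stop argues against progression unless modifiable barriers are found, and the team weighs the predominance of outcomes across eight criteria. Interviews on blinding add context.
- *Preoperative blinding cannot be measured.* The poll is meant to cover both periods. Its preoperative answer is retrospective and open to contamination, not absent.
- *The mirror-image pattern is to be expected.* A perceptible sham makes it plausible, but no document gives a guess rate.

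Poll timing is also a real trade-off, since an earlier question may make participants think about their allocation.

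**Conclusion.** The point holds as a defect in a stated decision rule. Equal belief in the active device in both groups is placed in Adjust once net belief (share guessing active minus share guessing sham) reaches 20 percentage points, and in Stop above 50 points. At Stop the verdict is the same as for real unmasking. The algebra holds for any guess rates that are equal in the two groups. The probabilities in Step 3 rest on assumed values of q, 70 respondents per device and no 'don't know' answers. The consequence is a risk of needless changes to the sham, or of blinding counting wrongly against progression, and not an automatic stop. The timing of the poll is secondary: it weakens the preoperative index, most of all in the two mixed arms, without making it uninformative.

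**What to change.** 1. In the Statistical analysis plan section, state that the index is calculated with a 95% CI separately for active and sham devices and separately for the preoperative and postoperative periods.
2. In the blinding row of Table 2, judge each active–sham pair jointly. Report mirror-image indices whose sum is about zero as shared belief or response bias, not as unblinding. Let Adjust or Stop be triggered by a positive index in either group that is not offset by an opposite-sign index in the other.
3. Fix in advance what counts as about zero, allowing for sampling error. Near random guessing with 70 per device and no 'don't know' answers, each index has a standard error of √(1/70) = 0.120, so the sum has √2 × 0.120 = 0.169 and a 95% half-width of 1.96 × 0.169 = 0.33.
4. Do not replace the rule by applying the present bands to the mean of the two indices (Step 5).
5. Consider asking the preoperative question on admission, when the first device is collected and before the second is used.

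The cost is a change of wording in two places and, for item 5, one question at an existing contact, with the small downside that it may prompt participants to think about allocation.
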